**Methods:**

Physical and social environmental interventions were developed by matching scientific evidence on environmental determinants of walking, with input from the target population and stakeholders, and ongoing neighbourhood activities. Specifically, a neighbourhood walking route was designed and marked, and neighbourhood walking groups were organised. These environmental interventions were evaluated in a four-armed experimental study. In addition, the design of the study to evaluate the effect of these environmental changes on walking behaviour is described.

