#### Route markings

The idea of the grass root organization with which we collaborated was to add art to the neighborhood, thereby making the neighborhood more colorful. Children of local primary schools could enter a competition by designing a 30 by 30 centimeter paving stone and by submitting the design (on paper) to the organization. The best designs were selected for a workshop in which the paving stones were painted. This process had already started before we initiated our collaboration. Together with the grass roots organization we extended this project within the neighborhood in which they started (Bloemhof) and extended this to other neighborhoods in which we planned a walking route.

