### Evaluation design, participants and recruitment

The environmental interventions are evaluated in a four-armed experimental study on changes in minutes walked. These four arms correspond to four neighbourhoods, namely: 1) a neighbourhood with the physical environmental intervention, 2) a neighbourhood with the social environmental intervention, 3) a neighbourhood with both physical and social environmental interventions and 4) a control neighbourhood (no interventions). These neighbourhoods were selected in close collaboration with policy makers on their comparability (demographics, physical environment). Although random allocation to study arms was envisaged, due to collaboration with ongoing activities assignment to the study arms was mostly based on practical reasons (e.g. the walking route project with which we collaborated started in one of the neighbourhoods; which became the physical environmental condition). Measurements will take place at baseline and 3 and 6 months after implementation of the environmental changes.

G*Power was used to perform a sample size calculation [49]. Because the aim of the intervention was to increase walking, our sample size calculations was based on the differences in the change in minutes walked, We used a repeated measures ANOVA design for this purpose, with four groups measured three times. We assumed a small effect size (f) of 0.1. In repeated measures, the correlation between the repeated measurements is also of importance, which we assumed to be 0.5, based on the reliability of the IPAQ (the instrument which was used to measure walking) [50]. Considering a power of 0.8 and a *p*-value of 0.05, a total sample size of 328 older adults is needed [49].

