To conclude, we described the development and evaluation of two interventions, one targeting the social neighbourhood environment and the other targeting the physical neighbourhood environment. The evaluation study will provide evidence for their separate and combined effects on walking behaviour of residents. Moreover, it will shed light in how changes to the environment may cause changes in walking behaviour.

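### The study is labelled experimental and promises evidence of effects, but with one neighbourhood per arm and practical, non-random assignment, an arm effect cannot be told apart from neighbourhood-specific change

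*Protocol article*

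**What the plan says.** The abstract states: "These environmental interventions were evaluated in a four-armed experimental study". The section Evaluation design, participants and recruitment repeats the label: "The environmental interventions are evaluated in a four-armed experimental study on changes in minutes walked". It then sets out the structure: "These four arms correspond to four neighbourhoods" (physical, social, both, and control).

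On allocation the same section is open: randomisation had been intended, but because the study joined existing local work, "assignment to the study arms was mostly based on practical reasons". Its single example is that "the walking route project with which we collaborated started in one of the neighbourhoods; which became the physical environmental condition". The section Route markings says of the paving-stone project: "This process had already started before we initiated our collaboration". It adds that the project was later extended to the other neighbourhoods where a route was planned.

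Two protections are described. The neighbourhoods were chosen for comparable demographics and physical environment, and the outcome is change from a baseline wave to two follow-up waves. Table 1 shows one wave before the interventions.

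The Discussion ends with: "The evaluation study will provide evidence for their separate and combined effects on walking behaviour of residents". Its next sentence says the study will inform how environmental change may cause changes in walking.

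**The concern.** The label and the conclusion claim more than the design can carry. The Background justifies the study by the limits of observational evidence and the need for insight into causality. In the physical arm, however, assignment followed existing local activity, and every arm consists of one neighbourhood. Anything else that happens in a neighbourhood between February/March and the follow-up waves (another local programme, a change in safety, carry-over from the earlier project) enters the estimate exactly as an intervention effect would.

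The direction of any bias is unknown. A neighbourhood that was improving anyway would make the route look effective; one whose baseline was already raised would hide an effect. At stake is whether a difference between arms may be reported as an effect of the route or the walking groups, or only as a difference between four places.

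**Working it through.** **Inputs.** From Evaluation design, participants and recruitment: 4 arms, 4 neighbourhoods, 3 measurement times, f = 0.1, correlation 0.5, power 0.8, α = 0.05, total N = 328. An equal split gives 328/4 = 82 per arm. The article gives no between-neighbourhood variance or trend, so those values below are assumptions shown as ranges.

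**The plan's own figure.** For the group-by-time interaction under sphericity, λ = N·m·f²/(1 − ρ) with df (k−1)(m−1) = 6 and (N−k)(m−1). The stated inputs then require N = 232, and power at N = 328 is 93%. So 328 is not reproduced from the stated inputs, though it is not too small for that test. This point does not depend on it; 328 is used only as the planned size. The calculation treats residents as independent and has no neighbourhood term.

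**Step 1: what the design can estimate.** Let P and S be the effects of the physical and social interventions, I their interaction, and d₁ to d₄ the changes that the physical, social, combined and control neighbourhoods would have shown without intervention. The expected mean changes are:

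- physical: P + d₁
- social: S + d₂
- combined: P + S + I + d₃
- control: d₄

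There are four means and four unknown drifts. Saturated model: 4 − 4 = 0 df for neighbourhood. Additive 2×2 model without I: 4 − 3 = 1 df, but then the combined arm cannot be tested for anything beyond the sum of its parts. The two available estimates of the physical effect are:

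- physical − control = P + (d₁ − d₄)
- combined − social = P + I + (d₃ − d₂)

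Subtracting a baseline removes stable level differences, which do not appear above. It leaves every d in place. With one pre-intervention wave, the d's cannot be checked against earlier trends.

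**Step 2: a fixed trend difference.** Take a difference δ in untreated change between two neighbourhoods, in SDs of the change score, with 82 residents each and no intervention effect. The probability that a two-sided 5% test declares an effect is Φ(δ/√(2/82) − 1.96) + Φ(−δ/√(2/82) − 1.96), where √(2/82) = 0.156.

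| δ (assumed) | δ/0.156 | P(declared effect) |
|---|---|---|
| 0.1 SD | 0.64 | 10% |
| 0.2 SD | 1.28 | 25% |
| 0.3 SD | 1.92 | 48% |

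Doubling to 164 per arm makes it worse: √(2/164) = 0.110, and δ = 0.2 gives Φ(1.81 − 1.96) ≈ 44%.

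**Step 3: random neighbourhood variation.** Let ICC be the share of change-score variance lying between neighbourhoods. The variance of an arm mean is s²[ICC + (1 − ICC)/82], whereas the person-level analysis uses s²(1 − ICC)/82. With r² the ratio of the two, the actual type I error is 2[1 − Φ(1.96/r)] for a pair of arms, and P(F₃,₃₂₄ > F_crit/r²) for the four-arm test. For ICC = 0.01: r² = (0.01 + 0.01207)/0.01207 = 1.83, r = 1.35, 1.96/1.35 = 1.45, giving 15%.

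| ICC (assumed) | pair of arms | four-arm F | lower limit of SE of a difference, √(2·ICC) |
|---|---|---|---|
| 0.001 | 6% | 6.5% | 0.045 SD |
| 0.005 | 10% | 13.5% | 0.10 SD |
| 0.01 | 15% | 23% | 0.14 SD |
| 0.02 | 23% | 40% | 0.20 SD |
| 0.05 | 40% | 69% | 0.32 SD |

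The last column is the limit as residents per neighbourhood grow without bound, so recruitment cannot buy it down.

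**The case against.** The non-random assignment is disclosed together with its reason, and the article never claims randomisation. The abstract and the Discussion both say that collaboration can constrain the evaluation. The neighbourhoods were chosen to be comparable, and the outcome is change. The concluding sentences speak of providing evidence and of what may cause change, which falls short of claiming proof. All of this is true, and it makes the matter one of labelling and inference, not concealment. It does not remove the problem. The Discussion's example of a constraint is the choice of route markers, and nowhere is one neighbourhood per arm named as a limit on causal inference. Comparability was sought on demographics and physical environment, not on local activity, which is what drove assignment in the example.

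Three stronger readings are tempting, and the documents do not support them.

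- *That the study plans no comparison able to help.* The article has no analysis section and the full plan is not shown, so this cannot be asserted. The four arms permit combined minus social, which does not use the neighbourhood where the project began, and GPS tracks and awareness and use items are planned.
- *That the physical neighbourhood was already mobilised to walk.* What is on record is a paving-stone design contest for schoolchildren and a route described as planned (Collaboration with stakeholders). Participants are aged 55 and above. No publicity or change in walking before baseline is reported. The example concerns one arm only; reasons for the others are not given.
- *That the two estimates of the physical effect should have to agree before an effect is claimed.* By Step 1 they differ by I plus drift terms. The Background motivates the study by synergy between trails and walking partners, so disagreement is what a successful combined intervention would produce. Each contrast also remains one neighbourhood against one.

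**Conclusion.** The point stands as a mismatch between design and claim. Arm and neighbourhood are completely aliased. That follows from the stated structure and needs no assumption, and no analysis plan could undo it for the four-arm comparison. Comparable selection and change from one baseline reduce some differences but leave neighbourhood-specific trends and concurrent activity in every contrast.

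The size of the resulting bias is unknown, as is its direction. The false-positive rates above (10% to 48% for an assumed trend difference of 0.1 to 0.3 SD; 6% to 40% per pair of arms for an assumed ICC of 0.001 to 0.05) show sensitivity and do not estimate what happened. They rest on 82 residents per arm, a normal approximation and a person-level analysis. The correction should be made, because it changes what the trial may conclude at almost no cost.

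**What to change.** 1. In the abstract and in Evaluation design, replace the experimental label with: non-randomised (quasi-experimental) controlled before-after study with one neighbourhood per arm.
2. In the Discussion, state that arm effects cannot be separated from neighbourhood-specific change, and that selection on comparability and a single baseline do not resolve this.
3. Limit the closing claim to differences in change between neighbourhoods that are consistent with an effect.
4. As supportive analyses only:
   - Report physical minus control and combined minus social side by side with confidence intervals, with no requirement that they agree, and note that those intervals do not include neighbourhood-level variation.
   - Within the two route neighbourhoods, relate change in walking to home-to-route distance, adjusted for baseline walking, resident characteristics and proximity to shops and facilities. State that this is not free of confounding: routes were drawn through facility hotspots, attractive sites were added and unattractive parts removed, and route guides went door to door across the neighbourhood, which blurs any gradient.

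**Cost.** Wording changes, modest extra analysis, and a more cautious conclusion. The distance analysis assumes that addresses from the register-drawn sample may be used for this purpose.

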Socio-ecological models suggest that interventions are likely to have the greatest effect when determinants at different levels are addressed simultaneously [24–26]. However, surprisingly little is known about the combined role of physical and social environmental characteristics on physical activity. Recent observational research confirmed however, that the availability of trails had a stronger influence on walking when walking partners were around [27]. Further, the availability of parks was more strongly associated with sports participation with increasing levels of neighbourhood social capital among youth [13]. While the limitations of observational evidence with regard to causal inference are generally recognized, the number of studies in which changes to the environment have been evaluated is still small [28]. For the ultimate purpose of creating walkable neighborhoods, more insight in causality is pivotal. Therefore, in the NEW.ROADS study, we aim to develop, implement and evaluate social and physical environmental interventions to promote walking behaviour among older adults living in deprived neighbourhoods. The current paper describes the development of these interventions and the design of the evaluation study, in which the separate and combined effects of the social and physical environmental interventions were tested.

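### The power paragraph sizes a four-group, three-time ANOVA at f = 0.1, which does not reproduce 328 and leaves the promised separate and combined effects without a stated detectable difference

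*Protocol article*

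**What the plan says.** All of the sizing is in the protocol article under *Evaluation design, participants and recruitment*. The target is the change in walking: "our sample size calculations was based on the differences in the change in minutes walked". The model is given as "We used a repeated measures ANOVA design for this purpose, with four groups measured three times". The effect size is "We assumed a small effect size (f) of 0.1". The correlation between repeated measurements is one "which we assumed to be 0.5, based on the reliability of the IPAQ". The result reads: "Considering a power of 0.8 and a *p*-value of 0.05, a total sample size of 328 older adults is needed".

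The same section lays out the arms: "These four arms correspond to four neighbourhoods, namely: 1) a neighbourhood with the physical environmental intervention", then one with the social intervention, one with both, and one control.

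The aim is stated twice. The *Background* says that "the separate and combined effects of the social and physical environmental interventions were tested". The *Discussion* closes with "The evaluation study will provide evidence for their separate and combined effects on walking behaviour of residents".

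The article gives no SD for weekly walking minutes, no target difference in minutes, no contrast to which the 80% power belongs, and no multiplicity rule.

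**The concern.** Physical only, social only, both and neither form a 2x2 layout. The questions in the aim are single contrasts within it: each intervention against none, and the two together. A group-by-time test over four unordered arms and three occasions has (4 − 1)(3 − 1) = 6 degrees of freedom. A significant result shows that the arms changed differently. It does not show which intervention worked or how the two combine.

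The size of f is a second difficulty. In this test f is a root-mean-square over twelve cells, so calling f = 0.1 small does not make the difference between two arms small. A reader of the paragraph could take the study to have 80% power for small effects of each intervention, and could then read a null result as evidence against such effects.

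**Working it through.** **Inputs.** From the article: 4 groups, 3 measurements, f = 0.1, correlation ρ = 0.5, power 0.8, α = 0.05, N = 328. My assumptions: equal arms (328/4 = 82), equal correlation between all pairs of occasions, independent residents, two-sided 0.05 without multiplicity allowance, and SD meaning that of a single measurement of weekly walking minutes.

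**1. Reproducing 328.** For the group-by-time interaction with k groups and m occasions, the noncentral F has λ = f²·N·m/(1 − ρ), df1 = (k − 1)(m − 1) and df2 = (N − k)(m − 1).

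| k x m | N | λ | df1, df2 | Power |
|---|---|---|---|---|
| 4 x 3 | 228 | 13.68 | 6, 448 | 0.795 |
| 4 x 3 | 232 | 13.92 | 6, 456 | 0.804 |
| 4 x 3 | 328 | 19.68 | 6, 648 | 0.934 |
| 2 x 3 | 164 | 9.84 | 2, 324 | 0.805 |

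The stated inputs therefore need 232. At 328 the test has 93% power for f = 0.1, or 80% power for f = 0.084. Other options with the stated inputs also miss 328: 164 for the time main effect, 732 for the between-group effect, and 692 or 688 under the alternative effect-size conventions. The number 328 can be reached by doubling the two-group result (2 x 164 = 4 x 82), by a nonsphericity correction of 0.6, or by inflating 164 for 50% dropout. The article states none of these.

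**2. What f = 0.1 means.** Take a gain d, in SD units, present at T1 and T2 and absent at T0. Then f = d x SD(arm pattern) x SD(time pattern). The time pattern (0, 1, 1) has SD 0.4714.

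| Pattern (control, physical, social, both) | SD of pattern | f | d at f = 0.1 | Omnibus power at d = 0.2, N = 328 |
|---|---|---|---|---|
| Additive (0, d, d, 2d) | 0.7071 | 0.333d | 0.30 (both arms combined: 0.60) | 57% |
| One component works, e.g. (0, d, 0, d) | 0.5000 | 0.236d | 0.42 | 29% |
| All three gain equally (0, d, d, d), or only the combined arm (0, 0, 0, d) | 0.4330 | 0.204d | 0.49 | 22% |

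**3. Sensitivity for the contrasts in the aim.** Use the mean of T1 and T2 minus T0. Its variance is σ²(0.75 + 1 − 2 x 0.5) = 0.75σ². The 80%-power difference is (1.96 + 0.84) x √(0.75c/82), where c = 2 for one arm against control, 1 for a 2x2 main effect and 4 for the physical-by-social difference of differences.

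| Contrast | Standard error (SD) | Detectable at 80% | Power at 0.2 SD |
|---|---|---|---|
| One arm against control | 0.135 | 0.38 SD | about 31% |
| Main effect of one component | 0.096 | 0.27 SD | about 55% |
| Physical by social | 0.191 | 0.54 SD | about 18% |

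On T2 minus T0 alone, the variance is σ² and the detectable differences rise to 0.44, 0.31 and 0.62 SD.

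**The case against.** **The study may not have been sized on the omnibus test.** A reader might infer from the four-group wording that 328 is the omnibus result. The arithmetic does not support that, since the omnibus needs 232. The match with 4 x 82 makes pairwise sizing plausible, but the text says four groups, so this too is inference. What stands is that the paragraph does not identify the test. Under pairwise sizing, f = 0.1 is still 0.42 SD for a sustained gain.

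**The stated power is not irrelevant to the aim.** This largely stands. One arm against control at 0.42 or 0.49 SD exceeds the detectable 0.38 SD, and an additive main effect of 0.30 SD exceeds 0.27 SD. It would be wrong to say that the power claim fails for every question asked. The gaps are effects near 0.2 SD, one arm against control at 0.30 SD (about 60% power), and the interaction. If all three arms gain equally by 0.49 SD, each main effect is also only 0.49/2 = 0.245 SD, just under 0.27.

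**Synergy is not a stated hypothesis.** A reader might infer one, because the *Background* cites evidence that trails and walking partners reinforce each other. But combined effects can mean no more than the combined arm against control, and no interaction test is promised. The 0.54 SD figure shows what the design can support; it does not show a broken commitment.

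**Uptake.** One might argue that effects must be diluted because few residents will use the route or the groups. The article gives no uptake figure, so the point does not rely on this.

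**More than 82 per arm may respond.** Approaching 700 per neighbourhood at 15–17% gives 105 to 119. The same formula then gives 0.33 to 0.31 SD (one arm against control) and 0.24 to 0.22 SD (main effect). No dropout rate is stated, so how much of this margin survives to T2 is unknown. It does not bring either figure down to 0.2 SD.

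**The analysis belongs in an analysis plan.** Agreed. A missing analysis section is not the complaint. The complaint is that the published sample size paragraph does not reproduce and is not connected to the published aim.

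**Conclusion.** The point holds in a limited form. The number 328 does not follow from the stated inputs for the test described: that test needs 232, and at 328 it has 93% power at f = 0.1. The effect labelled small corresponds to about 0.30 SD per component if effects add, 0.42 SD if one component works, and 0.49 SD if all three arms gain equally or only the combined arm gains. The sizing therefore does not cover a 0.2 SD effect: omnibus power there is 22% to 57%, and power for the single contrasts is about 31%, 55% and 18%.

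The documents do not support the broader conclusion that the separate effects are underpowered altogether. Moderate separate effects are adequately covered under the assumptions used.

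Those assumptions are 82 per arm, equal correlations of 0.5, a gain held at T1 and T2, and no multiplicity allowance. All contrast figures treat residents as independent. With one neighbourhood per arm, between-neighbourhood variation enters every contrast and cannot be separated from the intervention, so the powers are upper bounds.

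**What to change.** Rewrite the sample size paragraph in four respects.

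1. State the G*Power test option and every input that yields 328, including any nonsphericity correction or dropout allowance, or correct the number.
2. Describe the arms as the 2x2 they already form (physical, social and their product), and report each single-intervention arm and the combined arm against control.
3. Replace the single power sentence with the detectable difference for each of these contrasts, in SD units now and in minutes per week once an SD for walking minutes is stated with its source. Say that the figures assume independent residents.
4. Do not describe the study as powered for small separate or interaction effects.

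This costs wording and a short recalculation; it needs no new participants or data. There are two drawbacks. Main effects must be read together with the interaction, since they average over the other intervention. The stated sensitivity will also look less favourable than the present sentence suggests.

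### The total of 328 does not follow from the stated G*Power inputs: the group-by-time test needs 232, and at 328 its power is about 0.93 rather than 0.80

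*Protocol article*

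**What the plan says.** All of it is in the protocol article, section Evaluation design, participants and recruitment.

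- Software: "G*Power was used to perform a sample size calculation".
- Target: "our sample size calculations was based on the differences in the change in minutes walked".
- Design: "We used a repeated measures ANOVA design for this purpose, with four groups measured three times".
- Effect size: "We assumed a small effect size (f) of 0.1".
- Correlation between repeated measurements: "which we assumed to be 0.5, based on the reliability of the IPAQ".
- Error rates: power 0.8 and a significance level of 0.05.
- Result: "a total sample size of 328 older adults is needed", which is 328/4 = 82 per neighbourhood.

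The paragraph mentions no nonsphericity correction, multiplicity adjustment, design effect or dropout allowance. The expected response of 15-17% comes afterwards and is used only for the number of people to approach.

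**The concern.** The paragraph lists nearly everything G*Power needs for this procedure and presents 328 as what those inputs require. That is a checkable statement, and a reader who enters the inputs gets a different number. 328 is the only stated basis for the size of the study. If it cannot be regenerated, the reader cannot tell what power the study was planned to have for its own question, namely group differences in change. Nor can the reader tell which effect-size convention f = 0.1 refers to. That second point matters because the same f = 0.1 means very different effects under G*Power's different conventions.

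**Working it through.** **Inputs from the protocol article:** k = 4 groups, m = 3 measurements, f = 0.1, ρ = 0.5, α = 0.05, target power 0.80.

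**Assumption:** sphericity (ε = 1), because no other value is given. A single common correlation with equal variances implies it. N is taken in multiples of 4 so that groups are equal.

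**1. The test that matches the stated target.** Differences between groups in change are the group-by-time (within-between) interaction. In G*Power's default convention:

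- λ = f²·N·m·ε/(1 − ρ) = 0.01 × N × 3/0.5 = 0.06N
- df1 = (k − 1)(m − 1)ε = 6; df2 = (N − k)(m − 1)ε = 2(N − 4)

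| N | λ | df2 | Power |
|---|---|---|---|
| 228 | 13.68 | 448 | 0.795 |
| 232 | 13.92 | 456 | 0.804 |
| 328 | 19.68 | 648 | 0.934 |

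The required total is 232. The plan's figure is not reproduced.

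**2. The other repeated-measures options with the same inputs.**

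| Procedure | λ | df1, df2 | N for 0.80 | Power at 328 |
|---|---|---|---|---|
| Within factors | 0.06N | 2, 2(N − 4) | 164 | 0.98 |
| Between factors | f²·N·m/(1 + (m − 1)ρ) = 0.015N | 3, N − 4 | 732 | 0.43 |
| Interaction, SPSS convention | f²(N − k)(m − 1) = 0.02(N − 4) | 6, 2(N − 4) | 692 | 0.43 |
| Interaction, Cohen convention | f²·N(m − 1) = 0.02N | 6, 2(N − 4) | 688 | 0.44 |
| Within factors, SPSS or Cohen convention | as the two rows above | 2, 2(N − 4) | 488 or 484 | 0.62 |

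The multivariate (MANOVA) versions give 164 for the within test and 232 to 240 for the interaction. None of these gives 328.

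**3. What would give 328 for the interaction test.** Each route adds or changes one input:

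- ε = 0.6, everything else as stated: λ = 0.036N, df1 = 3.6, df2 = 1.2(N − 4). N = 324 gives 0.7995 and N = 328 gives 0.805, so the answer is exactly 328.
- ρ ≈ 0.285 in place of 0.5: λ = 0.03 × 328/0.715 = 13.76, power 0.800.
- An attrition allowance on 232: 232/0.71 = 326.8 and 232/0.70 = 331.4, so roughly 29-30% loss.

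The article states none of these, and they are not the same assumption.

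**4. Power of the interaction test at N = 328 for other correlations**, with λ = 9.84/(1 − ρ):

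| ρ | 0.5 | 0.4 | 0.3 | 0.2 |
|---|---|---|---|---|
| Power | 0.93 | 0.87 | 0.81 | 0.75 |

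**The case against.** The best defence is that nothing printed need be wrong. Nonsphericity is a separate entry in G*Power, and a value of 0.6 returns exactly 328 with every stated input and the stated test intact. A journal article condenses its protocol, so an omitted entry would be a reporting gap. This stands as far as it goes. It rules out the stronger inference that a printed input, or the named test, cannot be the one used. It does not rescue the number as written: one common correlation of 0.5 with equal variances implies no correction, so 0.6 would have to be stated. Other routes also reach 328 or its neighbourhood, and the text does not choose between them.

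A second defence is that the discrepancy is harmless. For the stated test in the default convention, 328 is more than is needed. The invitations also exceed what 328 requires: 82/0.15 = 547 per neighbourhood against about 700 approached, and 2,800 × 15-17% = 420 to 476 expected respondents. This lowers the importance of the point but leaves the arithmetic unresolved.

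Three further readings are tempting, and the documents do not support them.

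- A reader might infer that the study was really sized on the between-groups test, since another effect size can be found that returns 328. That is fitting backwards from the answer. It contradicts both the printed f and the stated target of change.
- A reader might infer that the study is underpowered, at about 0.43. That holds only under the between-groups test or the SPSS or Cohen convention, and the article names neither.
- A reader might argue that a correlation "based on the reliability of the IPAQ (the instrument which was used to measure walking") must be an upper bound over months and seasons. The article gives neither the reliability coefficient nor its retest interval, so 0.5 may already be a discounted value.

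**Conclusion.** The stated total is not reproducible from its stated inputs. For differences in change, with f in G*Power's default convention, sphericity and equal groups, the requirement is 232. The printed 328 is 96 more (328/232 = 1.41) and corresponds to power of about 0.93, not 0.80. An input is either unreported or different from the one printed, and the document does not settle which.

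Under the stated test with the default convention the error is on the safe side, so this should be fixed but does not undermine the study's size. At 328, power for that test stays at or above 0.80 down to a correlation of about 0.285 and is 0.75 at 0.2. All these figures treat residents as independent, with no allowance for clustering within neighbourhoods.

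**What to change.** Rerun the calculation and rewrite the one paragraph. Name the G*Power procedure (within-between interaction), the effect-size convention for f = 0.1, the nonsphericity value, the correlation entered and any inflation for attrition. Then do one of the following:

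- give 232 as the total for the inputs now listed; or
- keep 328 and state the power it provides: 0.93 at a correlation of 0.5, 0.87 at 0.4, 0.81 at 0.3 and 0.75 at 0.2.

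If an unreported input did produce 328, state it with its reason. The cost is one corrected paragraph. Recruitment and the number approached need not change.
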